**Objectives:**

The primary objectives are:

1. To describe the trends of paediatric TB cases identified over a 5-year period among children <15 years of age in rural and urban settings.
2. To describe the TB treatment outcomes among children < 15 years of age admitted with TB disease in rural and urban settings.
3. To identify risk factors that are present in children <15 years of age with active TB in rural and urban settings.

Specific Hypotheses to be Tested:

[figure not shown]

1. The number of diagnosed TB cases initiating therapy in rural and urban settings will decrease over time.
2. Length of hospital stay in days (LOS) for children with TB is longer in the rural setting vs the urban setting.
3. Mortality is higher among children with TB in the rural hospital setting vs the urban hospital setting.

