## **METHODS**

### **Study design**

Aims 1 and 2 are a retrospective study and historic cohort study design, respectively, collecting data on all forms of TB in the period of January 1, 2016 to June 30, 2021. Aim 3 is a descriptive cross-sectional study using a survey given to children with active TB, currently receiving treatment at an outpatient tuberculosis clinic.

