### **Study Procedures:**

#### Retrospective study and historic cohort study

We will perform a retrospective chart review of electronic and written medical records for 100 children <15 years of age who were diagnosed with TB at either Mulago National Referral Hospital or a Fort Portal Regional Referral Hospital in Uganda. Cases will be included between January 1, 2016 - June 30, 2021. The medical records will be reviewed, and eligibility will be confirmed through the inclusion and exclusion criteria. If the patient is eligible, the abstractor will proceed with a standardized chart abstraction form. If the patient is not eligible, the abstractor will look for an alternative case until the 100-patient sample is reached. Data elements to be extracted include: name, medical record number, date of birth, sex, address, nationality, ethnicity, hospital admission and discharge date, weight, height, diagnosis at admission, clinical symptoms at admission, date of symptoms onset, history of prematurity, birth weight, prior medical problems, BCG vaccination, history of TB contacts, prior history of TB infection, HIV infection status, CD4 count/percentage and viral load in HIV-infected, TB diagnostics (AFB, culture, PPD), radiographic imaging reports, biopsy reports, cerebral spinal fluid labs, major procedures or interventions, TB treatment regimen, treatment adverse reactions, anti-retroviral treatment regimen for HIV-infected, final diagnosis, discharge status, and follow-up recommendations. When available, data from the 12-month follow-up visit will also be abstracted.

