### **Study Statistics:**

#### Retrospective study and historic cohort study

The primary outcome variables are TB active case trends and treatment outcome at the time of hospital discharge. We will assess all available charts of pediatric patients admitted with active TB. Means and standard deviations (SD) for continuous variables, frequency and percentage for categorical variables will be used to summarize all predictor variables and the outcome variables. Comparisons of categorical variables will be made using Chi-square and comparison of continuous variables will be completed using independent t-tests or nonparametric tests depending on normality of distribution.

To test Hypothesis 1, that the number of diagnosed TB cases initiating therapy in rural and urban settings will decrease over time, we will fit a linear regression model with number of monthly cases diagnosed as outcome and study period (in months) as the predictor with the initial month of the study period (01-Jan-2016) represented as "1" and the final month of study period 06-Jun-2021 represented as "66", accepting a linear assumption that cases are evenly distributed across each month. We will further fit an interaction term in this regression model, between dichotomous TB diagnosis location (urban or rural) and continuous study period. In an alternative model, we will test for the bivariate correlation between the annual number of cases diagnosed and the year of diagnosis by computing the Pearson's correlation coefficient, with significant temporal trend defined as a  $p < 0.05$ . To test Hypothesis 2, that length of hospital stay in days (LOS) for children with TBM is longer in rural vs urban settings, we will fit a linear regression model with LOS as continuous outcome and location as dichotomous predictor, controlling for a-prior selected potential confounders. To test Hypothesis 3, that mortality is higher among children with TBM in the rural hospital setting vs the urban hospital setting, we will fit a multivariable logistic regression model with in-hospital mortality as dichotomous outcome and location as dichotomous predictor.

[figure not shown]

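### Hypothesis 1 has two tests of the same counts, no statement of which decides, and its only significance rule attached to the coarser annual test

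*Protocol*

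**What the plan says.** Objectives, Hypothesis 1: "The number of diagnosed TB cases initiating therapy in rural and urban settings will decrease over time". Study Statistics (retrospective and historic cohort part) names case trend as a primary outcome and gives the hypothesis two analyses of the same counts.

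- Monthly: "we will fit a linear regression model with number of monthly cases diagnosed as outcome and study period (in months) as the predictor", with months numbered 1 to 66. A location-by-time term follows: "We will further fit an interaction term in this regression model".
- Annual: "In an alternative model, we will test for the bivariate correlation between the annual number of cases diagnosed and the year of diagnosis", using Pearson's coefficient, "with significant temporal trend defined as a" p-value below 0.05.

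That threshold is the only significance definition in the paragraph, and it stands in the sentence on the annual correlation. Nothing says whether the annual analysis is a check, a replacement or a fallback. Sidedness is not given. Study design describes "collecting data on all forms of TB in the period of January 1, 2016 to June 30, 2021", so 2021 is a half-year, and the text does not say how it enters the annual counts.

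**The concern.** The protocol fixes two tests and one significance rule, but the parts point in different directions. The regression comes first, directly after the statement that Hypothesis 1 is being tested. The definition of a significant trend belongs to the correlation. A reader holding the results could defend either as the verdict.

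Two things are at stake. If either result may be reported as the trend, the error rate for a primary claim is above the level of one test. If cases really fall, the two tests will often disagree, and the plan gives no rule for choosing. Taking the annual p-value as the decider would also give up much of the information in the monthly data.

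**Working it through.** **Inputs from the protocol.** 66 months, made up of five full calendar years plus January to June 2021; threshold 0.05. The number of cases is 100 under Study Procedures ("the abstractor will look for an alternative case until the 100-patient sample is reached") or unspecified under Study Statistics ("We will assess all available charts of pediatric patients admitted with active TB").

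**Assumptions.** Two-sided tests. Independent Poisson monthly counts, without seasonality, overdispersion or autocorrelation. Totals of 100 to 3000 cases. Real falls are linear from the first month to the last.

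**Critical correlations.** The slope test and the Pearson test both use t = r·√[(n−2)/(1−r²)], so significance needs |r| > t/√(n−2+t²), with t the 97.5% point on n−2 degrees of freedom.

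- n = 66: t = 1.998, |r| > 0.242
- n = 6: t = 2.776, |r| > 0.811
- n = 5: t = 3.182, |r| > 0.878

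**No true trend.** The protocol states no combined error rate to reproduce. The either-test rate is P(monthly) + P(annual) − P(both). For 100 cases and five full years this is 5.0% + 4.9% − 1.3% = 8.6%. Two independent tests would give 1 − 0.95² = 9.75%. Simulation results (at least 100,000 data sets per row; ranges cover repeat runs and totals):

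| 2021 in the annual counts | Cases | Monthly alone | Annual alone | Either | Either, false decrease only |
|---|---|---|---|---|---|
| Dropped | 100–3000 | 5.0% | 4.9–5.1% | 8.5–8.8% | 4.2–4.4% |
| Doubled | 100–3000 | 5.0% | 6.1–6.3% | 8.7–8.9% | 4.4–4.5% |
| Half-year as it stands | 100 | 5.0% | about 10% | about 13% | about 10% |
| Half-year as it stands | 300 | 5.0% | about 10% | about 13% | about 10% |
| Half-year as it stands | 1000 | 5.0% | about 4% | about 8% | about 5% |
| Half-year as it stands | 3000 | 5.0% | 0.4% | 5.1% | 2.6% |

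The last four rows have a simple cause. With a constant rate and 100 cases, a full year expects 100 × 12/66 = 18.2 cases and the half-year 9.1. Five equal values followed by one of half the size have r = −0.65, short of the 0.811 needed. With small totals, chance variation often carries r past that limit. With large totals r stays near −0.65 and the test almost never rejects.

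**True linear fall.**

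| Cases, assumed fall | Monthly power | Annual power, five full years | Tests disagree |
|---|---|---|---|
| 100, 50% | 49% | 21% | 35% |
| 100, 70% | 88% | 44% | 46% |
| 500, 30% | 63% | 28% | 41% |

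With 2021 doubled, the annual power for the 100-case, 50% fall is about 36% and the tests disagree in 25% of runs. With the raw half-year it is about 56%, above the monthly 49%, but that test already rejects in about 10% of studies with no trend, so the comparison is not a fair one.

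**The case against.** The strongest reply is that the text already gives an order: the regression is introduced as the test of Hypothesis 1 and the correlation comes after it as an alternative. Main analysis plus supplementary check is a natural reading, and on it the error rate is 5%. Ranking such analyses is also often left to a statistical analysis plan. The placement of p < 0.05 may mean little, since no threshold is written beside the models for Hypotheses 2 and 3 either.

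Part of this stands. The protocol nowhere says that one significant result of the two is enough. A reader might infer that the plan carries a false-positive rate of 8.5 to 9%. The document does not support that as a property of the plan: it needs the either-counts reading, two-sided tests, and 2021 dropped or annualised, none of which is stated. For a false claim of a decrease, which is what Hypothesis 1 asserts, the either-test rate with five full years is about 4.4%, still under 5%.

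What does not fall away is that the protocol attaches its one definition of a significant trend to the analysis it calls the alternative. That is a rule put in the wrong place, and more than a detail left for later. An analysis plan that made the regression decisive would have to depart from that sentence.

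It is also fair to say that Objective 1 is worded as descriptive, and that if charts are picked until 100 are found the counts may not measure a trend under any test. The second is a separate problem, which this point does not resolve.

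**Conclusion.** The point holds in a conditional form. The absence of a named deciding test, and a threshold tied to the annual correlation, can be read directly from the protocol and need no assumption. The size depends on the reading.

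- Either test may decide, 2021 dropped or annualised: about 9% for a trend in either direction; about 4.4% for a false decrease, against 2.5% for one test.
- Half-year 2021 used as it stands: from about 13% at 100 cases to 5% at 3000. The annual test alone is then at about 10% with 100 cases, so making it the decider would not be safe.
- Monthly test alone: 5.0% at every total examined.

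Frequent disagreement under a real fall does not depend on the either-counts reading, though its size rests on the assumed falls and on independent Poisson counts. This should be corrected, but it does not threaten the study as a whole.

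**What to change.** State that the time coefficient of the monthly model is the single deciding test of Hypothesis 1 at two-sided 0.05, and move the p < 0.05 definition to it. Say that this coefficient comes from the model without the location-by-time term, because once that term is added it describes one location only. Keep the annual correlation as a descriptive sensitivity summary (r with a 95% confidence interval) with no significance claim, using full years only or an annualised 2021, and state which.

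The cost is two or three sentences and no extra data. The small downside is losing a second chance at a significant result.

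### The alternative annual trend test for Hypothesis 1 ends on a six-month 2021 with no stated adjustment, which biases the correlation toward the hypothesised decrease

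*Protocol*

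**What the plan says.** Hypothesis 1 (Protocol, Objectives) is directional: "The number of diagnosed TB cases initiating therapy in rural and urban settings will decrease over time". The data window is given under Study design ("collecting data on all forms of TB in the period of January 1, 2016 to June 30, 2021") and again under Study Procedures ("Cases will be included between January 1, 2016 - June 30, 2021").

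Study Statistics names two analyses for this hypothesis:

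- First, a monthly model: "we will fit a linear regression model with number of monthly cases diagnosed as outcome and study period (in months) as the predictor". Months are coded 1 to 66, and a site-by-time interaction is added.
- Second, introduced as an alternative model, a test of the "bivariate correlation between the annual number of cases diagnosed and the year of diagnosis" using Pearson's coefficient, "with significant temporal trend defined as a" p-value below 0.05.

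The annual analysis uses raw counts. The protocol does not scale 2021 to twelve months, exclude it, or turn counts into rates. It also does not say in so many words that 2021 enters the series; that follows from applying the sentence to the stated window.

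**The concern.** A raw annual count is comparable between years only if each year is observed for the same time. Here five years have twelve months and the last has six. The short year sits at the end of the series, where a single point has most influence on a slope, and it is low for a reason unrelated to disease. The artefact runs in the direction of Hypothesis 1.

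Active case trend is one of the primary outcome variables in Study Statistics, and the protocol gives no rule for the case where the monthly and annual analyses disagree. With flat data the monthly model would tend to show nothing while the annual coefficient would usually be negative, and a reader could take the second as support for the hypothesis.

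**Working it through.** **Inputs.** Window 1 January 2016 to 30 June 2021 (Study design); months coded 1 to 66, Pearson's r and p < 0.05 (Study Statistics); 100 charts (Study Procedures). Assumed: Poisson counts, both sites pooled, no seasonality, a two-sided test, and 2021 entered as its raw count.

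**The plan's own figure.** 5 × 12 + 6 = 66 months, which matches the protocol's coding and fixes 2021 as a six-month year.

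**Constant rate.** Expected annual counts are proportional to y = (12, 12, 12, 12, 12, 6), with mean 11 and deviations (1, 1, 1, 1, 1, -5). Centred years are x = (-2.5, -1.5, -0.5, 0.5, 1.5, 2.5).

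- Sxx = 17.5; Syy = 5 × 1 + 25 = 30; Sxy = -2.5 + (2.5 × -5) = -15.
- r = -15 / √(17.5 × 30) = -15 / 22.91 = -0.655.
- t = -0.655 × √(4 / (1 - 0.429)) = -1.73 on 4 df, two-sided p = 0.16.
- Slope = -15 / 17.5 = -0.857 per year for 66 cases, or -0.857 × 100/66 = -1.3 cases per year for 100 charts, all of it due to the half year.
- Significance with six points needs |r| > 0.811, so the flat series on its own does not reach it.

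**Growth that still gives a negative r.** With yearly growth factor q and equal months within a year, the slope is zero when -2.5 - 1.5q - 0.5q² + 0.5q³ + 1.5q⁴ + 1.25q⁵ = 0, which gives q = 1.093. With growth compounding month by month the break-even is 9.5% per year. On the expected counts (monthly compounding), 5% growth gives r = -0.33 (p = 0.52), and 20% growth gives only r = 0.51 (p = 0.30).

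**False declines at a constant rate** (200,000 simulated studies per row):

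| Total cases | r < 0 | Significant decline, raw 2021 | 2021 doubled | 2016-2020 only |
|---|---|---|---|---|
| 50 | 84% | 8.2% | 3.2% | 2.4% |
| 100 | 92% | 9.8% | 3.2% | 2.4% |
| 200 | 98% | 10.2% | 3.2% | 2.5% |
| 500 | 99.9% | 7.7% | 3.2% | 2.5% |
| 1000 | 100% | 4.2% | 3.1% | 2.5% |
| 5000 | 100% | 0.0% | 3.2% | 2.5% |

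Nominal is 2.5% in this direction. The rate falls at large totals because r settles near -0.655, short of the 0.811 threshold.

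**True growth, 100 cases:**

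| Growth per year | Significant decline, raw | Significant increase, raw | Significant increase, 2021 doubled |
|---|---|---|---|
| 5% | 2.9% | 0.1% | 9.9% |
| 10% | 0.7% | 0.5% | 23.3% |
| 15% | 0.1% | 1.5% | 41.2% |

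**Monthly regression, 100 flat cases** (50,000 simulated studies): significant declines in 2.5%, so the half year does it no harm.

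**The case against.** The strongest reply is that the affected test is labelled an alternative, while the monthly regression comes first and handles the half year correctly. That stands, and it lowers the severity. The p < 0.05 criterion appears only in the Pearson sentence, and a reader might infer that the annual test is therefore the decisive one. The text does not support this: no significance level is written beside Hypotheses 2 and 3 either.

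A reader might also infer that flat or rising case numbers will be reported as declining. The protocol's criterion is p < 0.05, not the sign of r. A flat series gives p = 0.16 on the expected counts, about 90% of flat studies of 100 cases are not called declining, and real growth is mostly hidden rather than reversed with significance.

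It can be said, too, that nothing states 2021 is counted as a full year, that Objective 1 speaks of five years, and that a SAP could settle a partial year. Objective 1 leaves room for five complete years but does not say which, and every stated window runs to 30 June 2021. The protocol has already fixed outcome, predictor, statistic and threshold, and that combination gives a biased result if followed.

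Finally, the error rates depend on the number of cases. Study Procedures fills a quota of 100 charts, whereas Study Statistics speaks of assessing all available charts; counts from a filled quota need not be Poisson. This is fair, so the rates are given over a range. The constant-rate r = -0.655 does not depend on the total.

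**Conclusion.** The point holds for the alternative annual analysis. Applied to the stated window, it biases r toward Hypothesis 1: -0.65 at a constant rate, and negative on the expected counts up to about 9% true growth per year. Under the stated assumptions, false significant declines are about three to four times nominal for 50 to 500 cases, with less inflation at 1000 and none at 5000. True increases are largely masked. The documents do not support the stronger claim that flat or rising numbers would generally be declared a significant decline, nor any claim against the monthly regression. Severity: should be fixed before analysis, as a flaw in a supporting test of a primary outcome.

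If the final month's printed date of 6 June 2021 were a real cut-off, the last point would be smaller still; the other sections say 30 June.

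**What to change.** State that the monthly model is the test of Hypothesis 1, and reword the annual sentence in one of two ways:

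- use complete years only, either calendar years 2016-2020 or five July-June years from July 2016 to June 2021; or
- model annual counts by Poisson or negative binomial regression with log(months observed) as offset (12, 12, 12, 12, 12, 6).

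The annual test need not be deleted. With so few points, a descriptive role suits it.

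The cost is one sentence and no new data. Complete years leave six months out of the annual summary (January-June 2021 or January-June 2016), though the monthly model still uses them. The offset keeps every month but assumes that January-June is typical of a whole year.

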Sample size calculations to determine the appropriate number of retrospective charts to review are based on Hypothesis 2 using the t-statistic as calculated at [quesgen.com](http://quesgen.com). We will test associations between hospital setting and outcomes (LOS and mortality) in the entire cohort of children with active tuberculosis. Testing our Hypothesis 2,  $n=100$ , we are adequately powered at  $> 80\%$  to detect differences in LOS outcome of  $> 16$  days, an adequate effect size as LOS for children with active TB is typically several weeks (median 36 days, IQR 21-60 days in the (Blount 2014) cohort).

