## REQUEST FOR WAIVER OF INFORMED CONSENT

Project Title: **Tuberculosis Risk Factors and Outcomes among Children in Urban and Rural Uganda**

**Principal Investigator:** [name], medical student  
**Faculty Mentor(s):** [name], paediatrician  
[name], physician-scientist

**Research Team Contact:** [name]: [contact] (cell); [contact]

The researcher plans to determine the prevalence of tuberculous meningitis and discharge outcomes in rural vs urban hospitals in Uganda.

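### The Study Statistics section words the tests of Hypotheses 2 and 3 for children with TBM, while the hypotheses, eligibility, sample size and stated test cohort cover all active TB; the power figure does not carry over to a TBM-only analysis

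*Protocol*

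**What the plan says.** The places that bear on the analysis population do not agree.

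- **Objectives.** Hypothesis 2 reads "Length of hospital stay in days (LOS) for children with TB is longer in the rural setting vs the urban setting". Hypothesis 3 reads "Mortality is higher among children with TB in the rural hospital setting vs the urban hospital setting". Neither is limited to meningitis.
- **Study design and Inclusion criteria.** Aims 1 and 2 collect every form of TB, and both pulmonary and extra-pulmonary cases are eligible.
- **Study Statistics, model paragraph.** Hypothesis 2 is restated as "that length of hospital stay in days (LOS) for children with TBM is longer in rural vs urban settings", to be tested by linear regression. Hypothesis 3 is restated as "that mortality is higher among children with TBM in the rural hospital setting vs the urban hospital setting", to be tested by logistic regression.
- **Study Statistics, sample size paragraph.** The association of hospital setting with both outcomes is to be tested "in the entire cohort of children with active tuberculosis". The 100 charts and the power of more than 80% for differences above 16 days rest on Hypothesis 2.
- **Request for Waiver of Informed Consent.** The purpose is given as to "determine the prevalence of tuberculous meningitis and discharge outcomes in rural vs urban hospitals in Uganda". The research plan directly below it returns to 100 children with active tuberculosis. The prevalence of TB meningitis is not among the Objectives.

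**The concern.** The model paragraph is the only text that sets out the models for Hypotheses 2 and 3, and it names TBM in both. The repetition makes it hard to dismiss as one stray letter. The waiver request and two meningitis-specific exclusion criteria could encourage a reader to take it at face value.

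TBM is one form of the disease that the study enrols, so a TBM-only analysis would use fewer than the 100 charts unless every chart were TBM. It would also answer a narrower question than the Objectives ask. Two things are at stake. First, an analyst could cite the protocol for either population, which weakens its value as a record of what was planned before the data were seen. Second, the power statement for length of stay would not describe a TBM-only test.

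**Working it through.** **Inputs from the protocol's sample size paragraph:** 100 charts in total; a difference of 16 days; power above 80%; a t-statistic; a cited cohort with median stay 36 days and IQR 21 to 60.

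**Assumptions, because the protocol gives no figure:** two-sided alpha 0.05; charts split equally between urban and rural; SD obtained from the IQR by the normal relation; the same SD in TBM as in all TB; a TBM share of the charts varied from 10% to 75%.

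**Step 1. SD.** SD = (60 − 21) / 1.349 = 28.9 days.

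**Step 2. Reproduce the stated power in the full cohort.** With n = 50 per setting, the standard error of the difference is 28.9 × √(2/50) = 5.78 days. The noncentrality is 16 / 5.78 = 2.77. With 98 degrees of freedom the noncentral t gives power of 78.2%; the normal approximation gives 79.0%. The difference detectable with 80% power is 16.4 days (t) or 16.2 days (normal). A one-sided test gives about 87%. The protocol's figure is therefore approximately right for all TB, which indicates that the sizing was done for the full cohort. It has almost no slack: two-sided power of 80% for 16 days needs an SD of at most 28.3 (t) to 28.6 (normal) days.

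**Step 3. Same calculation in a TBM subset.** With share f, n per setting = 100f / 2 and the noncentrality is 16 / (28.9 × √(2/n)). Noncentral t, two-sided 0.05:

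| TBM share | n per setting | Noncentrality | Power for 16 days | Difference detectable with 80% power |
|---|---|---|---|---|
| 100% (full cohort) | 50 | 2.77 | 78% | 16 days |
| 75% | 37.5 | 2.40 | 66% | 19 days |
| 50% | 25 | 1.96 | 48% | 23 days |
| 30% | 15 | 1.52 | 31% | 31 days |
| 20% | 10 | 1.24 | 22% | 38 days |
| 10% | 5 | 0.88 | 12% | 59 days |

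**Step 4. Sensitivity to the SD.** The spread of stay in TBM is not given. At a 50% share (25 per setting), power for 16 days is 79% with SD 20, 60% with SD 25, 48% with SD 28.9 and 35% with SD 35.

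**Step 5. Hypothesis 3.** The protocol claims no power for mortality, so there is nothing to recompute. The fault there is only the mismatch of populations.

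**The case against.** The strongest reply is that the protocol does state the analysis population, and that it is all TB. The sample size paragraph, in the same section, names both disputed outcomes and assigns them to the full active-TB cohort. The model paragraph itself begins by committing to assess every available chart of children admitted with active TB. TBM appears only in the clauses that restate the hypotheses; the model specifications define no TBM subset, and its size is given nowhere. The line in the waiver request is a summary outside the analysis plan, corrected by the text that follows it.

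Most of this stands. A reader might infer that the plan, run as written, is a TBM-only analysis and that its power claim collapses. The document does not support that: the power claim is tied to the full cohort, where it approximately reproduces. Nor can any loss be stated as a single figure, since it turns on a TBM share and an SD that the protocol does not give. A reader might also extend the power argument to mortality, but the protocol makes no such claim for Hypothesis 3.

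The reply does not remove the contradiction. The sentences that introduce the two models name a different population from the Objectives and from the sample size paragraph, and nothing says which prevails. That the weight of the text favours all TB shows which way to correct it, not that no correction is needed.

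**Conclusion.** The point holds as a contradiction in the analysis population for Hypotheses 2 and 3. It should be settled before any analysis, because it concerns which children enter two of the three hypothesis tests.

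The consequence for power is conditional and limited to Hypothesis 2. For the full cohort the figure is about 78% against a stated value above 80%, which is close enough to accept given the unstated SD, alpha and split. With those assumptions held and a common SD, any restriction to a TBM subset lowers power further, from about 66% at a 75% share to about 12% at 10%. A smaller SD in TBM would soften the loss and a larger one would deepen it. The wording of the waiver request is a secondary inconsistency.

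**What to change.** In the model paragraph of Study Statistics, change TBM to TB in the sentences for Hypothesis 2 and Hypothesis 3, so that the analysis set is the entire active-TB cohort, as in the Objectives and the sample size paragraph. In the Request for Waiver of Informed Consent, align the stated aim with the Objectives.

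If a TBM analysis is really intended, define that population, state the expected number of TBM charts per setting and the spread of their length of stay, and restate the power for it.

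The first route costs only wording and needs no new data. Adjusting the models for form of TB is optional; the contradiction is resolved without it. If it is wanted, final diagnosis and cerebrospinal fluid results are already on the abstraction list.
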